### 3.5.1. Schedule

- Screening: reporting and presurgical visit
- Baseline visit (V1) 7 to 10 days before surgery
- Visit V2 (K0 or K1 postoperative)
- Visit V3 (day of discharge: K4 - K7 postoperative)
- Immediate postoperative visit (V4): 14+/- 2 days following surgery
- Postoperative visit (V5): 28+/- 4 days following surgery
- Follow-up visits at two months (V6)

### 3.5.2. Visit schedule

- Screening: reporting and presurgical visit
  - Check for compliance with inclusion and non-inclusion criteria
  - Explanation of the trial to the patients
  - Issue of the Patient Information Letter
- Baseline visit (V1) 7 to 10 days before surgery:
  - Consent form signed
  - Injection of pasireotide or placebo
  - Recording of adverse events
  - ECG
  - Blood sample for pharmacokinetic monitoring
- Visit V2 (K0 or K1 postoperative): collection of data concerning the operation (type of surgery, duration, intraoperative complications, type and number of drains)
  - Recording of adverse events:
- Visit V3 (day of discharge: K4 - K7 postoperative) Summary of the daily collection of postoperative data:
  - The daily and total drainage volumes
  - Date on which drains were removed and overall duration of drainage
  - Postoperative complications (hematoma, skin necrosis, etc.)
  - Whether aspiration of a symptomatic lymphocele was required
  - Length of hospital stay
  - Recording of adverse events:

It has been decided that drains will be removed when the daily drainage volume is less than 50 cc and that the maximum total duration of drainage will be 7 days. The drain will be emptied as from the 5th postoperative day.

- Immediate postoperative visit (V4): 14+/- 2 days following surgery. If the V4 visit corresponds to more than 24 days after injection, this visit will be advanced in order to perform ECG and pharmacokinetic between 19 and 23 days after injection of pasiréotide LAR.
  - The number of repeated lymphocele aspirations and the volume (patients requiring an aspiration will be seen during the interval between two consultations at the hospital and data will be colligated in the medical file. To ensure the lymphoceles sufficiency, a free phone number will be given to the patient in order that she could report any event if necessary.)
  - Recording of adverse events
  - Blood sample for pharmacokinetic monitoring
  - ECG
- Postoperative visit (V5): 28+/- 4 days following surgery
  - Routine lymphocele aspiration is considered positive if the volume aspirated exceeds 120cc.
  - The number of repeated lymphocele aspirations and the volume.
  - Adjuvant chemotherapy starting date, if required
  - Recording of adverse events:
- Follow-up visits at two months (V6)
  - Recording of adverse events:

### 3.5.3. Evaluation criteria

#### 3.5.3.1. Endpoints

**Primary endpoint**

The primary endpoint of this study is the ratio of patients who did not have symptomatic, postoperative axillary lymphoceles defined as the absence of aspiration or a unique or iterative aspirations global volume of lymphoceles inferior to 60cc inclusive (≤) in the 28 days after the intervention or a systematic aspiration volume at the 28th day inferior to 120cc inclusive (≤)

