# 1. Introduction

Octreotide, a somatostatin analog, has demonstrated its efficacy in the medical management of postoperative gastro-intestinal and pancreatic fistulae. Two recent studies have shown its value in reducing lymphoceles following axillary node dissection performed as part of breast cancer surgery.

The principal morbidity following axillary node dissection within the scope of breast cancer surgery is the postoperative development of lymphocele following the removal of an axillary drain. This may be a source of pain, repeated aspiration, infection and delayed local healing.

Pasireotide, a somatostatin analog under evaluation and possessing a high affinity for somatostatine receptors (30 to 40 times greater for sst1 and sst5 receptors, 5 times greater for sst3 and equivalent for sst2) is an attractive molecule in this indication.

Based on the encouraging results published with octreotide and the greater effects anticipated with pasireotide, we want to assess the benefit of preoperative administration of pasireotide in reducing the incidence of axillary lymphoceles following mastectomy - axillary node dissection.

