## 3.5. Visits and evaluations

| ***Tests*** | ***Screening*** | ***Inclusion*** | **Day** | | | **Month** | |
| --- | --- | --- | --- | --- | --- | --- | --- |
| *Visits* |  | ***V1 = D1*** | ***V2*** | ***V3*** | **V4**8 | **V5** | **V6** |
| *Days* |  | *K-10 to K-7* | *K0 - K1* | *K4 to K7* | K12 to K16 | K24 to K32 | K60 |
| *Trial information* | X |  |  |  |  |  |  |
| *Inclusion - non-inclusion criteria* | X |  |  |  |  |  |  |
| *Informed consent form* |  | X |  |  |  |  |  |
| *Randomization* |  | X |  |  |  |  |  |
| *Demographic data, history of the tumor, medical and surgical history1*. |  | X |  |  |  |  |  |
| *Neodjuvant treatment* |  | X |  |  |  |  |  |
| *Injection of prolonged release pasireotide or placebo* |  | X |  |  |  |  |  |
| *Clinical evaluation, signs and symptoms 2* | X | X | X | X | X | X | X |
| *Adverse events 3* |  | X | *X* | *X* | *X* | *X* | *X* |
| *Surgical data 4* |  |  | X |  |  |  |  |
| *Postoperative data 5* |  |  |  | X |  |  |  |
| *Clinical evaluation 6* |  |  |  | X | X | X | X |
| *Permanent anatomopathological characteristics and adjuvant treatments 7* |  |  |  |  |  | X |  |
| *Routine lymphocele aspiration* |  |  |  |  |  | X |  |
| *Laboratory blood tests (pharmacokinetics)* |  | X |  |  | X |  |  |
| *ECG* |  | X |  |  | X |  |  |

1: demographic data (age, BMI), tumor history, medical and surgical history (breast surgery), concomitant medical diseases (diabetes, obesity), neo-adjuvant chemotherapy, tumor characteristics (TNM classification, histology, location)

2: weight, blood pressure, heart rate, fever.

*3: examination for skin reactions at the injection site (redness, pain, necrosis) and other adverse events.*

*4: type of procedure, duration, complications during surgery, compression dressing, type, number and location of drains.*

*5: daily and total drainage volume, date on which drains are removed and total drainage volume, postoperative complications (hematoma, skin necrosis, abscess, fever), presence of a lymphocele, lymphocele aspiration and duration of hospital stay.*

*6: number of lymphocyte aspirations, volume aspirated on each occasion, adjuvant chemotherapy start date. Skin test: redness, delayed healing, abscess, leakage.*

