## 6.2. Efficacy evaluation:

The evaluation criterion will be the proportion of patients who did not have symptomatic, postoperative axillary lymphoceles defined as the absence of aspiration or a unique or iterative aspirations global volume of lymphoceles inferior to 60cc inclusive (≤) in the 28 days after the intervention or a systematic aspiration volume at the 28th day inferior to 120cc inclusive (≤).

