## 6.5. Primary endpoint analysis

The statistical analysis will be carried out sequentially after observing the principal criterion (i.e. success is defined as a total volume of lymphoceles following single or repeated aspiration ≤ 60 cc in the 28 days following surgery or a routine aspiration volume on the 28th day ≤ 120cc) of each patient included for each randomization group, with or without treatment.

It involves estimating the probability of a response in each group (proportion of patients who will not have undergone lymphocele aspiration or the aspiration of a total volume of ≤ 60cc or ≤ 120cc for the aspiration carried out on the 28th day after surgery) using a Bayesian design based on a beta-binomial model (16,17). With the Bayesian approach, the response rate in each group (*i*) is considered as a random variable *primarily* of density focused on the anticipated response rate of 80% in the group receiving treatment and 60% in the treatment-free group, which will be sequentially updated as the observations are made according to a so-called *a posteriori* law.

*A priori* density will be selected for each group from the Beta conjugated laws group, defined by its two parameters *ai*and *bi* (with a life expectancy = and variance = , with *i=1,2* according to the group considered). The Bayesian estimator of the response rate in each group will be expectancy of the *a posteriori* law, i.e. the Beta law of parameters *Ani* and *Bni* , defined on the basis of those of the *a priori* law and the number *ni* of inclusions, as shown below. *Ani=a+ri* and *Bni=b+ni-ri,* where *ri* represents the number of responses observed on the *ni* included in the *i* group. The following estimator is, therefore, obtained: .

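### The primary endpoint counts only needle aspiration, so a lymphocele evacuated by another procedure can be scored as a success

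*Protocol*

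**What the plan says.** Protocol section 2.1 sets the objective: to reduce the incidence of symptomatic axillary lymphoceles after mastectomy with axillary node dissection.

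The endpoint that stands for this objective is given in the Summary, in 3.5.3.1, in 6.2 and in 6.5, each time in terms of aspiration:

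- 3.5.3.1: success is "defined as the absence of aspiration or a unique or iterative aspirations global volume of lymphoceles inferior to 60cc inclusive (≤") over 28 days, or a systematic day-28 aspiration of no more than 120 cc.
- 6.2: "The evaluation criterion will be the proportion of patients who did not have symptomatic, postoperative axillary lymphoceles defined as the absence of aspiration", followed by the same volume limits.
- 6.5, the response as analysed: "proportion of patients who will not have undergone lymphocele aspiration or the aspiration of a total volume of ≤ 60cc or ≤ 120cc", the last limit applying to the day-28 aspiration.
- 3.5.2, visit V5: "Routine lymphocele aspiration is considered positive if the volume aspirated exceeds 120cc".

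Elsewhere the protocol recognises that a lymphocele can show itself in other ways. The Introduction says of lymphocele: "This may be a source of pain, repeated aspiration, infection and delayed local healing". Note 5 to the table in 3.5 (visit V3) records "postoperative complications (hematoma, skin necrosis, abscess, fever), presence of a lymphocele, lymphocele aspiration". Note 6 (V3 to V6) adds "Skin test: redness, delayed healing, abscess, leakage". The Summary lists local healing, infections and fever among the secondary endpoints; the list in 3.5.3.1 keeps only febrile episodes.

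On drains, 3.5.2 covers only the initial one (the closing figure is in days): "drains will be removed when the daily drainage volume is less than 50 cc and that the maximum total duration of drainage will be 7". The protocol does not say how a later drain or a surgical evacuation is to be classified.

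**The concern.** The objective is about lymphoceles; the endpoint is about one way of emptying them. Where a collection is emptied by another procedure, the endpoint records the absence of an aspiration and reads it as the absence of a symptomatic lymphocele. This is a classification that the stated rule produces, not a detail left open for later.

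Two things are at stake. First, false successes come out of the failures. If the drug works, there are more failures to lose under placebo, so the measured difference shrinks. Second, section 6.6 judges the response rate against fixed limits of 60% and 80% and decides on inclusions group by group. False successes that are equally common among the failures of both arms therefore do not cancel there: they move each arm away from the inefficacy rule and towards the efficacy rule.

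**Working it through.** **Step 1: apply the definition to a case.** Take a woman whose initial drain is out and whose lymphocele becomes infected and is opened around day 15. No needle aspiration is done, and at V5 (K24 to K32) the routine aspiration yields little.

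| Limb of the definition | Her status |
|---|---|
| No aspiration, or total at most 60 cc in 28 days | met |
| Routine day-28 aspiration at most 120 cc | met |
| Symptomatic lymphocele in the sense of 2.1 | present |

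She meets both volume limits, so she is a success whether they are joined by *or* or by *and*. The V5 aspiration is a real but partial safeguard: it finds only fluid that is still there or has re-formed.

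**Step 2: effect on the rates.** Inputs from 6.4 and 6.5: anticipated success of 60% in controls and 80% on treatment, 45 patients per arm. The share m of true failures evacuated by another procedure, with no aspiration above the limits, is not in the protocol; 5% to 15% is assumed, with 30% as an extreme.

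Observed success rate = p + (1 − p) × m.

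| m | Control | Treated | Difference | False successes per 45 (control / treated) |
|---|---|---|---|---|
| 0 | 60% | 80% | 20 points | 0 / 0 |
| 5% | 62% | 81% | 19 points | 0.9 / 0.45 |
| 10% | 64% | 82% | 18 points | 1.8 / 0.9 |
| 15% | 66% | 83% | 17 points | 2.7 / 1.35 |
| 30% | 72% | 86% | 14 points | 5.4 / 2.7 |

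For scale, the standard error of the difference at 60% and 80% is √(0.60 × 0.40/45 + 0.80 × 0.20/45) = 0.094, or 9.4 points. A loss of 1 to 3 points is small beside that.

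**Step 3: effect on the stopping limits.** The protocol gives no values for the prior parameters, so several were assumed: Beta(1,1) for both criteria, priors centred on 80% for criterion 2 (Beta(0.8,0.2), (4,1), (8,2)) and priors centred on 60% for criterion 1 (Beta(0.6,0.4), (3,2), (6,4)). With r successes among 45, the posterior is Beta(a + r, b + 45 − r).

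| Criterion | Successes | Probability across the four priors | Against 0.90 |
|---|---|---|---|
| 2: P(rate > 80%) | 39 | 0.84 to 0.895 | continue |
| 2: P(rate > 80%) | 40 | 0.92 to 0.95 | stop, efficacy |
| 1: P(rate < 60%) | 22 | 0.91 to 0.94 | stop, inefficacy |
| 1: P(rate < 60%) | 23 | 0.86 to 0.89 | continue |

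At the boundary, one reclassified patient changes the decision. This shows sensitivity, not likelihood: with 39 true successes there are 6 failures, and one of them is 1/6 = 17%, just above the assumed range; with 22 true successes there are 23 failures, and one is 1/23 = 4%, just below it.

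**The case against.** The strongest reply is that aspiration is a deliberate yardstick. The definition is aspiration-based wherever it appears. Section 3.2 ties the 40% incidence to symptomatic lymphocele aspiration, and women who need an aspiration between visits are seen at the hospital and have a free phone line. The affected subset is also narrow: no aspirated total above 60 cc, relief by another procedure, and no more than 120 cc back at V5. The protocol does not mention re-drainage or surgical evacuation, so their frequency is unknown, and coding of rare events is often left to other documents. All of this bears on size, and it stands. It does not remove the point, because the protocol itself fixes the rule, and the rule gives the wrong answer for these patients.

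Two stronger readings are tempting. One is that the drug could look better than it is by turning aspirated lymphoceles into infected ones. With no true effect, 40% incidence in both arms and all such cases on pasireotide, the false benefit would be 0.40 × (5% to 15%) = 2 to 6 points. The documents do not support that pattern: section 1.2 describes hyperglycaemia as potential and transient and says nothing of infection or healing. Infections and healing are also secondary endpoints in the Summary, so such a shift could be seen by arm. It remains a possibility only.

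The other is that wound leakage should itself be a failure. Note 6 records leakage without a volume and without linking it to a lymphocele. A slight ooze would then fail while a 60 cc aspiration succeeds, which is subjective and inconsistent.

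**Conclusion.** The concern holds for procedural evacuation. By every statement of the primary endpoint, a patient whose symptomatic lymphocele is evacuated by a new drain, by incision or surgery, or by opening an abscess of it can be counted as free of symptomatic lymphocele, contrary to the objective in 2.1.

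The expected effect is modest: a slight dilution of the difference (1 to 3 points out of 20 if 5% to 15% of failures are affected equally in both arms) and a small upward shift of each arm's rate against the 60% and 80% limits. Both figures rest on an assumed share that the protocol neither gives nor bounds. A reader might infer that the most serious lymphoceles are in general scored as successes. That goes too far: anyone aspirated beyond the limits, or with more than 120 cc at V5, is still meant to be a failure. The change is worth making because it costs little and aligns the endpoint with the objective.

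**What to change.** In the Summary (both the endpoint and the statistical analysis paragraphs), 3.5.3.1, 6.2 and 6.5, add one sentence: a patient is also a failure if, between removal of the initial drain and the V5 routine aspiration, an axillary lymphocele was evacuated by any procedure other than needle aspiration (new drain, incision or surgical evacuation, opening of an abscess of the lymphocele), as classified by the blinded team.

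Do not count wound leakage by itself as failure; report it by arm as a secondary outcome.

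Add one CRF item for re-drainage or surgical evacuation. Notes 5 and 6 in section 3.5 record abscess and leakage but not these procedures.

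Cost: one sentence in each place and one CRF item. There will be a few more failures in both arms, and the endpoint departs slightly from the aspiration-based 40% incidence behind the anticipated 60% and 80%. The change concerns outcome classification only; clinical care is untouched.

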The side effects described with pasireotide include potential transient, post-prandial, dose-dependent hyperglycemia, which mainly appears as from the administration of injections of 600g. Intestinal disorders have been reported (diarrhoea, nausea and vomiting) but do not generally warrant medication since they spontaneously disappear as treatment continues.

In the literature, the incidence of axillary lymphoceles following surgery for breast cancer varies considerably: a recent meta-analysis of 66 studies revealed an incidence of 4 to 89 % depending on whether or not drainage was being carried out, the type of surgery (conservative or not), the time at which the drain was removed and whether or not a compression dressing was applied.

In our experience, the incidence at Hôpital Tenon is 40%. This percentage has been corroborated by Gustave Roussy Institute data, which recorded an incidence of 39.3% in out of 70 patients who underwent surgery between November 2008 and February 2009.

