## 6.4. Number of subjects

A total of 90 patients will be included over 12 months with 45 patients in the treatment group and 45 patients in the treatment-free group. In principle, there is no need to justify the number of subjects in a Bayesian study (15). However, the concept of desired accuracy of the success rate can be used based on its distribution a posteriori to define a test sample to be included.

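### The primary endpoint joins its two volume limits with *or*, so a large symptomatic lymphocele before day 28 counts as a success if the routine V5 aspiration is small

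*Protocol*

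**What the plan says.** The primary endpoint is defined in the Summary of Protocol and in sections 3.5.3.1, 6.2 and 6.5. Section 3.5.3.1 first gives "absence of aspiration or a unique or iterative aspirations global volume of lymphoceles inferior to 60cc inclusive (≤) in the 28 days after the intervention", then adds a separate limit of 120 cc for the routine day-28 aspiration, joined by *or*: "in the 28 days after the intervention or a systematic aspiration volume at the 28th day inferior to 120cc inclusive". Section 6.5 presents the same rule as the definition of success: "≤ 60 cc in the 28 days following surgery or a routine aspiration volume on the 28th day ≤ 120cc". Nowhere are both limits required.

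The visit descriptions in sections 3.1.2 and 3.5.2 say of V5: "Routine lymphocele aspiration is considered positive if the volume aspirated exceeds 120cc". The table in section 3.5 lists "Routine lymphocele aspiration" at V5, in a window of K24 to K32, without restricting it to a subgroup.

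Section 6.5 centres the priors on an "anticipated response rate of 80% in the group receiving treatment and 60% in the treatment-free group". Section 6.6 uses the same 60% and 80% as fixed thresholds for stopping inclusions in each group.

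**The concern.** Joined by *or*, either limit is enough for success. A patient can exceed the 60 cc limit by any amount and be rescued by a small volume at V5. The primary objective in section 2.1 is to reduce the incidence of symptomatic lymphocele, so the endpoint would count some patients with that event as free of it.

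Two consequences follow. Success rises in both arms, so the 60% and 80% thresholds no longer describe the quantity being measured. And because section 6.5 analyses the data sequentially as each patient's outcome is observed, an unclear rule affects stopping decisions during the trial as well as the final table.

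**Working it through.** **1. Logic.** Let E be the non-routine (symptomatic) volume in the 28 days after surgery and V the routine V5 volume. The protocol does not say whether V counts toward the 60 cc total, so both readings are shown.

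| E (cc) | V (cc) | *or*, V not counted (or V5 at K29–K32) | *or*, V counted (V5 by K28) | *and*, V not counted |
|---|---|---|---|---|
| 400 (at K14) | 0 | success | success | failure |
| 0 | 300 | success | failure | failure |
| 0 | 100 | success | success, though the 60 cc limit is broken | success |
| 400 | 300 | failure | failure | failure |

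The first row is a success under either reading of *or*. The second row depends on the reading. Where it is a success, it conflicts with the V5 rule, which calls 300 cc positive. In the third row, if V is counted, the two limits disagree about the same fluid (any V of 61–120 cc). That does not change the result under *or*, but it would once both limits are required.

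If V is counted and V5 falls by K28, a total of at most 60 cc already implies V ≤ 120 cc. The *or* rule then reduces to V ≤ 120 cc alone, and the 60 cc limit does nothing.

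**2. Source of the 60%.** Section 1.2 reports that "the incidence at Hôpital Tenon is 40"%, and 1 − 0.40 = 0.60. Treating this 40% as the placebo chance of E > 60 cc is an assumption, because the protocol gives it as an incidence of lymphocele without a volume limit.

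**3. Placebo success, V not counted.** Let a = P(E > 60) = 0.40, q = P(V > 120), and j = the probability of both.

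- *or*: success = 1 − j
- *and*: success = 1 − (a + q − j)

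The protocol does not give q, so 10–40% is assumed. j comes from a bivariate normal with latent correlation ρ.

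| q | *or*: ρ = 0 / 0.5 / 0.8 | *and*: ρ = 0 / 0.5 / 0.8 |
|---|---|---|
| 10% | 96 / 92 / 90% | 54 / 58 / 60% |
| 20% | 92 / 86 / 82% | 48 / 54 / 58% |
| 30% | 88 / 81 / 75% | 42 / 49 / 55% |
| 40% | 84 / 76 / 70% | 36 / 44 / 50% |

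Example: q = 20%, ρ = 0 gives j = 0.40 × 0.20 = 0.08, so *or* = 0.92 and *and* = 1 − 0.52 = 0.48. If V is counted and V5 falls by K28, *or* success is simply 1 − q, that is 90% down to 60%.

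**4. Treatment difference.** Assume treatment lowers early failure from 40% to 20% and leaves q unchanged. The first limit alone then shows 20 points. Under *or* the difference is about 2 to 12 points over the same grid. Since P(A or B) + P(A and B) = P(A) + P(B), the *and* difference is 20 minus that, about 8 to 18 points. *And* does not always give the larger difference: at q = 40%, ρ = 0.8, *or* gives 12.2 and *and* gives 7.8.

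**5. Stopping rule.** Criterion 2 declares efficacy when the posterior probability of a rate above 80% exceeds 0.90. For the control arm, take a Beta prior with mean 0.60 and an assumed weight of 1 to 5 patients. At n = 45 this needs 40 or 41 successes. The chance of meeting it at that single look is:

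- true rate 0.70: below 0.01
- true rate 0.80: 0.04–0.09
- true rate 0.88: 0.36–0.54
- true rate 0.96: 0.97–0.99

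**The case against.** The strongest defence is that the sentence is a list of limits by type of aspiration: none; up to 60 cc for aspirations during the 28 days; up to 120 cc for the routine one. The parenthesis in section 6.5 ties each limit to its own aspiration, the V5 rule calls more than 120 cc positive, and a 60% control rate suggests the planners did not expect near-ceiling success. This is a plausible account of intent, and nothing shows that the sponsor chose the literal rule on purpose. But it means that intent and text differ wherever the endpoint is defined, and no section says that both limits must hold.

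A reader might infer two stronger claims. The first is that a large volume at V5 alone always counts as a success. It does so only if the routine aspiration is left out of the first limit or is done at K29–K32; otherwise 300 cc breaks every limit and she fails. The second is that placebo success must already be at or above 80%, leaving the thresholds meaningless. That rests on assuming 10–20% over 120 cc at V5. At 30% the *or* rate is 75–88%, and at 40% it is 70–84%. The documents support miscalibrated thresholds of unknown extent, and no more.

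**Conclusion.** The endpoint is wrong as written. The early-lymphocele case (400 cc at K14, nothing at V5) is a success under either reading of the 28-day total and contradicts the primary objective; this depends on no assumed figure. The place of the routine aspiration in the 60 cc total is unresolved, and on one reading the endpoint contradicts the V5 rule.

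The direction of the effect is clear: the literal rule cannot give a success rate below that of the first limit alone. The size is not known from the protocol. The ranges of about 70–96% (*or*) and 36–60% (*and*) for placebo rest on 40% early failure, an assumed 10–40% over 120 cc at V5, latent correlation 0 to 0.8, and the routine volume not being counted in the first limit. The smaller treatment difference further assumes that treatment does not change the V5 failure rate. The case for *and* is that it measures the stated objective, not that it always gains power.

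**What to change.** In the Summary and in sections 3.5.3.1, 6.2 and 6.5, state that success requires both:

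- (a) no non-routine (symptomatic) aspiration, or a cumulative non-routine volume of at most 60 cc, in the 28 days after surgery, whether before or after V5; and
- (b) a routine V5 aspiration (K24–K32) of at most 120 cc, or no collection.

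State that the routine V5 volume does not count toward the 60 cc total, and align the V5 rule in sections 3.1.2 and 3.5.2 with this definition. Counting non-routine aspirations after V5 matters: with V5 at K24, a symptomatic aspiration at K26 would otherwise be missed. Handling of a missing V5 can be left to the SAP.

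Then confirm that the 60% and 80% anticipated rates and the thresholds in section 6.6 refer to this joint endpoint.

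The cost is one definition reworded in four places and a check of the priors and thresholds. The protocol already collects the number and volume of aspirations, so no new data are needed. The downside is that the anticipated control rate may have to be restated somewhat below 60%, since the joint rule is stricter than the first limit alone.
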